## Treatments and rationale for dose selection

Test product:

28 days preoperatively (± 3 days): Discontinuation of all local antiglaucomatous drugs and IOP regulation with COSOPT-S® (dorzolamide/timolol, MSD) eye drops b.i.d. (7:00 am, 7:00 pm; +/- 1 h) four weeks preoperatively.

Reference therapy:

Preoperative standard management of the Department of Ophthalmology, University Medical Center Mainz:

28 days preoperatively (± 3 days): Discontinuation of all local antiglaucomatous drugs and IOP regulation with oral acetazolamide 250 mg - 1500mg per day (two or three doses); potassium monitoring and potassium replacement if required.

7 days preoperatively (±1 day): Preservative-free dexamethasone 1mg/ml eye drops five times per day

The dosing frequency is based on that of the individual marketed products.

## Summarized risk-benefit assessment

All medicinal products which are used in this study have been used in daily practice for many years. The potential risks and benefits of the test products can be assumed to be identical to those described in the Summary of Product*.* The investigator will be informed about any relevant or new finding including AEs relating to treatment with the investigational medicinal product.

# Trial Objectives

## Primary objective

The primary objective of the trial is to investigate mean IOP reduction (∆IOP) three months after trabeculectomy in comparison to the mean preoperative IOP at Visit 1.

## Secondary objectives

The secondary objective(s) of the trial are:

- Safety and tolerability of both treatment arms: Analysis of adverse events and questionnaires.
- Number of necessary 5FU injections and suture lyses at Visit 5
- Required number of needlings and reoperations at Visit 5
- Change in IOP between Visit 1 and Visit 2
- Comparison between both groups of ocular hypotension rate (IOP 0-5 mm Hg, shallow anterior chamber, Descemet’s folds, choroid swelling, macular and choroidal folds) and filtration bleb classification in both groups at every postoperative visit
- Change in quality of life for the two regimens based on the NEI VFQ 25 quality-of-life questionnaire between Visit 1, Visit 2 and Visit 5 in both groups
- Patients’ satisfaction with pharmacologic intervention for IOP lowering between Visit 1, Visit 2 and Visit 5 in both groups
- Change in the conjunctiva status between Visit 1 and Visit 2 in both groups

# Trial Design

A prospective, active-controlled, open-label, randomized monocentric parallel group study including 60 patients.

## Trial duration and schedule

The duration of this trial is expected to be 14 months. The subject recruitment proposed to start beginning of July 2010 and end in January 2011. Last patient last visit will be achieved approximately in August 2011. However, the actual overall trial duration or subject recruitment period may vary from this time period.

## Number of subjects

It is planned to enrol 60 subjects in the clinical trial, i.e. 30 subjects per treatment group (1:1 ratio)*.* Recruitment and treatment of subjects is expected to be performed in one trial center.

## Primary endpoint

The primary objective of the trial is to investigate mean IOP reduction (∆IOP) three months after trabeculectomy (Visit 5) in comparison to the mean preoperative IOP at Visit 1.

## Secondary endpoints

- Safety and tolerability of both treatment arms: Analysis of adverse events and questionnaires.
- Number of necessary 5FU injections and suture lyses at Visit 5
- Required number of needlings and reoperations at Visit 5
- Change in IOP between Visit 1 and Visit 2
- Comparison between both groups of ocular hypotension rate (IOP 0-5 mm Hg, shallow anterior chamber, Descemet’s folds, choroid swelling, macular and choroidal folds) and filtration bleb classification in both groups at every postoperative visit.
- Change in quality of life for the two regimens based on the NEI VFQ 25 quality-of-life questionnaire between Visit 1, Visit 2 and Visit 5 in both groups
- Patients’ satisfaction with pharmacologic intervention for IOP lowering between Visit 1, Visit 2 and Visit 5 in both groups based on a visual analogue scale
- Change in the conjunctiva status between Visit 1 and Visit 2 in both groups

## Measures taken to minimize/avoid bias

In order to minimize potential bias toward the outcome of this study regarding the safety, efficacy or comfort of the test articles, patients will be randomly assigned to receive the test product or the reference therapy in the treatment phase.

### Randomisation

Patients will be randomised to COSOPT-S b.i.d. or standard therapy. Randomisation lists will be generated by IZKS Mainz by means of a computer program. The treatment allocation will be performed using central randomisation (FAX/Online or equal). The randomisation list will be kept in safe and confidential custody at the Interdisziplinäres Zentrum Klinische Studien (IZKS), Klinikum der Johannes Gutenberg-Universität, [name].

### Blinding

Not applicable.

## Selection and withdrawal of subjects

No subject will be allowed to enrol in this trial more than once. Patients will be selected according to the inclusion and exclusion criteria. An elaborate informing conversation will be followed by sufficient time for making the decision. Subjects are free to discontinue the trial at any time without giving any reason.

### Inclusion criteria

Subjects meeting all of the following criteria will be considered for admission to the trial:

- Male or female patients aged 18 years or older
- Caucasian
- A clinical diagnosis of open angle glaucoma, pseudoexfoliation or pigment dispersion glaucoma, or ocular hypertension in one or both eyes
- Planned trabeculectomy
- Previous treatment with antiglaucoma agents containing preservatives for at least one month
- Best corrected visual acuity of 20/800 or better in the study eye
- Ability of subject to understand character and individual consequences of clinical trial.
- Signed and dated informed consent of the subject must be available before start of any specific trial procedures.
- Women with childbearing potential have to practicing a medically accepted contraception during trial and a negative pregnancy test (serum or urine) should be existent before trial Reliable contraception are systematic contraceptives (oral, implant, injection) and dia-phragm or condoms with spermicide. Women that are sterile by surgery or for more than two years postmenopausal can be participate in the trial.

### Exclusion criteria

Subjects presenting with any of the following criteria will not be included in the trial:

- Secondary glaucoma except pseudoexfoliation glaucoma and pigmentary glaucoma
- Current ocular infection, i.e. conjunctivitis or keratitis
- Any abnormality preventing reliable applanation tonometry
- Intraocular surgery or laser treatment within the past three months
- History of surgery involving the conjunctiva
- History of cataract surgery with sklerocorneal approach
- Subject is allergic to sulfonamides
- Reactive airway disease, including bronchial asthma or a history of bronchial asthma, or severe chronic obstructive pulmonary disease
- Sinus bradycardia, second or third degree atrioventricular block, overt cardiac failure, cardiogenic shock
- Severe renal dysfunction (CrCl < 30 ml/min) or hyperchloraemic acidosis
- Depressed blood levels of sodium and / or potassium
- Marked kidney and liver disease or dysfunction, gout, suprarenal gland failure, hypercalciuria or nephrocalcinosis
- History of hypersensitivity to the investigational medicinal products or to any drug with similar chemical structure or to any excipient present in the pharmaceutical form of the investigational medicinal products
- Participation in other clinical trials during the present clinical trial or within the last four weeks
- Medical or psychological condition that would not permit completion of the trial or signing of informed consent
- Pregnancy and lactation

A pregnancy test will be performed in women with childbearing potential prior to randomisation. Laboratory tests including all relevant values mentioned in the exclusion criteria will be performed if no current values are available.

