| IOP | Intraocular Pressure |
| ISF | Investigator site file |
| ITT | Intention to treat |
| KKS | Coordination Center for Clinical Trials (Koordinierungszentrum für Klinische Studien) |
| LKP | Clinical Trial Director according to AMG (Leiter der Klinischen Prüfung) |
| LSI | Last subject in |
| LSO | Last subject out |
| MedDRA | Medical dictionary for regulatory activities terminology |
| OCT | Optical Coherence Tomography |
| SAE | Serious adverse event |
| SAP | Statistical analysis plan |
| SDV | Source data verification |
| SUSAR | Suspected unexpected serious adverse reaction |
| TMF | Trial master file |

Synopsis

| Title | Investigation of the efficacy and safety of preoperative IOP reduction with preservative-free COSOPT-S® (dorzolamide/timolol, MSD) eye drops versus oral acetazolamide and dexamethasone eye drops and assessment of the clinical outcome of trabeculectomy in glaucoma patients |
| --- | --- |
| Short title | COSOPT-S®  Study |
| EudraCT | 2010-019975-30 |
| Sponsor trial code | 35131 |
| Indication | Glaucoma requiring trabeculectomy |
| Phase | IV |
| Treatments | Test product: COSOPT-S® (dorzolamide/timolol, MSD) eye drops b.i.d.  Reference therapy: oral acetazolamide 250 mg - 1500mg (DIAMOX®) per day (two or three doses), Preservative-free dexamethasone 1mg/ml eye drops five times per day |
| Primary objective | - To demonstrate that COSOPT-S® b.i.d is not inferior to the standard regimen in terms of IOP reduction three months after trabeculectomy. |
| Secondary objectives | - To show that the tolerability and safety of COSOPT-S® b.i.d. is descriptively superior to that of reference therapy - Comparison of the regimen COSOPT-S® b.i.d. with the reference regimen in terms of postoperative complications and the filtration bleb status three months after trabeculectomy - Exploration of patients’ satisfaction |
| Trial design | A prospective, active-controlled, open-label, randomized monocentric parallel group study |

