# TRIAL Treatments

## Investigational treatments

**Test product:**

28 days preoperatively (± 3 days): Discontinuation of all local antiglaucomatous drugs and IOP regulation with COSOPT-S® (dorzolamide 20mg/ml and timolol 5mg/ml, MSD) eye drops b.i.d. (7:00 am, 7:00 pm; +/- 1 h)

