**Reference therapy:**

Preoperative standard management of the Department of Ophthalmology, University Medical Center Mainz:

28 days preoperatively (± 3 days): Discontinuation of all local antiglaucomatous drugs and IOP regulation with oral acetazolamide 250 mg - 1500mg per day (two or three doses, dosis depending on IOP); potassium monitoring and potassium replacement if required.

7 days preoperatively (±1 day): Preservative-free dexamethasone 1mg/ml eye drops five times per day

All patients will be assigned to receive either test product or reference therapy formulations as per the randomization schedule. Both treatment phases have duration of four weeks. Treatment with study medication will be discontinued at the end of the study. The investigator will give the total quantity for the treatment phase of the investigational product to the eligible subject at visit 1. At the inclusion visit, each subject will be explained in detail the mode of administration of the test product and reference therapy, as well as a follow-up notebook in which the subject should report any deviations from the stipulated frequency of application, any problems of local tolerability, any adverse reactions, and any comments related to the study that he/she may wish to add.

If the subject is unable to read, the legally acceptable representative, according to the subject’s opinion, should fill in the follow-up notebook. At the last visit, all the investigational medicinal products (full, half-used or empty) must be returned to the investigator. If the products are not returned, the investigator will question the subject to determine the reason for this.

At each visit, any change in the frequency of administration of the test product will be recorded in the Case Report Form. This evaluation will be based, in particular, on the data recorded in the follow-up notebook given to each subject.

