There have been reports of bacterial keratitis associated with the use of multiple-dose containers of topical ophthalmic products. Patients who, in most cases, had a concurrent corneal disease or a disruption of the ocular epithelial surface had inadvertently contaminated these containers. Choroidal detachment has been reported with administration of aqueous suppressant therapy (e.g., dorzolamide) after filtration procedures.

**Acetazolamide** is a sulphonamide like dorzolamide. Systemic side effects correspond to dorzolamide.

**Timolol:** Minor side effects of timolol include abdominal cramps, [diarrhea](http://www.medicinenet.com/script/main/art.asp?articlekey=24711), [constipation](http://www.medicinenet.com/script/main/art.asp?articlekey=331), fatigue, [insomnia](http://www.medicinenet.com/script/main/art.asp?articlekey=47466), [nausea](http://www.medicinenet.com/script/main/art.asp?articlekey=24732), and [vomiting](http://www.medicinenet.com/script/main/art.asp?articlekey=101642). Major side effects include [depression](http://www.medicinenet.com/script/main/art.asp?articlekey=342), vivid dreams or [memory loss](http://www.medicinenet.com/script/main/art.asp?articlekey=63547), [fever](http://www.medicinenet.com/script/main/art.asp?articlekey=361), [impotence](http://www.medicinenet.com/script/main/art.asp?articlekey=24721), lightheadedness, slow heart rate or [low blood pressure](http://www.medicinenet.com/script/main/art.asp?articlekey=1950), numbness, tingling, cramps, blueness of the hands or feet, [sore throat](http://www.medicinenet.com/script/main/art.asp?articlekey=480), and [shortness of breath](http://www.medicinenet.com/script/main/art.asp?articlekey=34434) or wheezing.

Side effects of **dexamethasone** depend on the dose, the duration and the frequency of administration. Short courses of dexamethasone usually are well tolerated with few and mild side effects. Long term, high dose dexamethasone usually will produce predictable and potentially serious side effects. Whenever possible, the lowest effective dose of dexamethasone should be used for the shortest possible length of time to minimize side effects. Alternate day dosing also can help reduce side effects.

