### Overdose instructions

Application of study medication should be stopped immediately.

**Dorzolamide hydrochloride** and **acetazolamide**: Electrolyte imbalance, development of an acidotic state, and possible central nervous system effects may occur. Serum electrolyte levels (particularly potassium) and blood pH levels should be monitored.

**Timolol:** No specific data are available at present. Expected reactions include bradycardia, hypotension, bronchospasms, acute cardiac failure, vomiting, numbness and cramps.

**Dexamethasone:** Overdose reactions did not occur so far.

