## Assessment of safety

### Adverse events

#### Definitions

Adverse Event (AE)

According to GCP, an adverse event (AE) is defined as any untoward medical occurrence in a subject treated with a pharmaceutical product and which does not necessarily have a causal relationship with this treatment. An AE can therefore be any unfavourable and unintended sign (including an abnormal laboratory finding), symptom, or disease temporally associated with the use of a medicinal investigational product, whether or not related to that product.

An AE may be:

a new symptom or medical condition

a new diagnosis

a change in laboratory parameters

an intercurrent illness or accident

worsening of a medical condition/diseases existing before the start of the clinical trial

recurrence of a disease

an increase in frequency or intensity of episodic diseases.

Surgical procedures themselves are not AEs; they are therapeutic measures for conditions that require surgery. The condition for which the surgery is required may be an AE. Planned surgical measures permitted by the clinical trial protocol and the condition(s) leading to these measures are not AEs, if the condition leading to the measure was present before inclusion in the trial. In the latter case the condition should be reported as medical history.

Change in laboratory parameters: The criteria for determining whether an abnormal test finding should be reported as an adverse event are as follows:

- Test result is associated with accompanying symptoms, and/or
- Test result requires additional diagnostic testing or medical/surgical intervention, and/or
- Test result leads to a change in trial dosing outside of protocol-stipulated dose adjustments, or discontinuation from the trial, significant additional concomitant drug treatment, or other therapy, and/or
- Test result is considered to be an adverse event by the investigator or sponsor.

Merely repeating an abnormal test, in the absence of any of the above conditions, does not constitute an adverse event. Any abnormal test result that is determined to be an error does not require reporting as an adverse event.

Change in symptoms asked in the questionnaires:

Changes in a symptom asked in the symptom survey/questionnaire will be documented as an AE if the symptom worsened at least three grades (grade 1-10). Grade 0 corresponds to no complaints.

Serious adverse event (SAE)

A serious adverse event (SAE) is one that at any dose (including overdose):

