### Prior and concomitant treatments

Relevant additional treatments administered to the subjects on entry to the trial or at any time during the trial are regarded as concomitant treatments und must be documented on the appropriate pages of the CRF. Potassium replacement might be necessary in the reference group.

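### Adverse events found by potassium testing can arise mainly in the reference arm and are pooled with symptom-based events, and no visit in either arm records pulse or blood pressure despite the named timolol risks

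*Protocol*

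**What the plan says.** **Safety aim.** The protocol synopsis lists as a secondary objective: "To show that the tolerability and safety of COSOPT-S® b.i.d. is descriptively superior to that of reference therapy". Sections 2.2 and 3.4 name safety and tolerability of both arms without giving a direction.

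**Laboratory follow-up.** The reference regimen (sections 1.3, 4.1 and 4.1.3) includes "potassium monitoring and potassium replacement if required". The test regimen, "IOP regulation with COSOPT-S® (dorzolamide 20mg/ml and timolol 5mg/ml, MSD) eye drops b.i.d", has no counterpart. Section 6.3.2 adds: "Potassium replacement might be necessary in the reference group". The schedule table has laboratory tests at Visit 1 only, where applicable, and section 3.6.2 requires them only when no current values exist. Section 5 lists none at Visits 2 to 6.

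**From test result to AE.** Section 6.2.1.1 gives several criteria, any one of which makes a laboratory finding an AE. One is "Test result requires additional diagnostic testing or medical/surgical intervention, and/or". Section 7.4 then counts patients with one or more AEs by MedDRA class and term, subdivided by intensity and relationship to drug, with a full listing.

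**Cardiovascular risk.** Section 3.6.2 excludes "Sinus bradycardia, second or third degree atrioventricular block, overt cardiac failure, cardiogenic shock". Section 4.1.2 puts slow heart rate and low blood pressure among the major effects of timolol. Section 4.1.4 says of timolol overdose: "Expected reactions include bradycardia, hypotension, bronchospasms, acute cardiac failure, vomiting, numbness and cramps". Neither the schedule table nor section 5 lists pulse, blood pressure or an ECG at any visit.

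**The concern.** A comparison of AE counts is fair only if events are looked for equally in both arms. Here one arm has a planned blood test whose abnormal results can become AEs, and the other has none. The protocol does not treat the test drug as free of systemic effects: section 4.1.2 says dorzolamide is absorbed systemically and says of acetazolamide, "Systemic side effects correspond to dorzolamide". If low potassium occurred on Cosopt-S without symptoms, it would usually go unrecorded.

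The cardiovascular gap is of a different kind. Pulse and blood pressure are unscheduled in both arms alike, but the effects that go unmeasured are those the protocol names for timolol, which is study medication only in the test arm. Both gaps tend to make Cosopt-S look safer. What is at stake is the descriptive safety statement, which has only raw counts to rest on. The primary non-inferiority analysis is not affected.

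**Working it through.** **1. Inputs.** There are 30 patients per arm (section 3.2). The protocol gives no rate of low potassium, potassium replacement or any AE under the study regimens as combined here, so it has no figure of its own to reproduce on this point. All rates below are assumptions.

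**2. Does potassium replacement count as an AE?** On a plain reading of section 6.2.1.1, yes, because replacement is a medical intervention prompted by a test result. The carve-out for dose adjustments laid down in the protocol stands in a different criterion and concerns trial dosing.

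**3. Splitting the recorded difference.** Let p_R and p_T be the true proportions of patients with a laboratory event that would qualify, and s_R and s_T the proportions of these that are detected. The expected difference in recorded patients is

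30(p_R·s_R − p_T·s_T) = 30(p_R − p_T)·s_R + 30·p_T·(s_R − s_T).

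The first term is a real drug effect. The second is ascertainment. It depends on the test arm's true rate and cannot exceed 30·p_T:
- p_T = 5%, s_R = 1, s_T = 0: 30 × 0.05 = 1.5 patients (5 percentage points)
- p_T = 10%: 30 × 0.10 = 3 patients (10 points)
- p_T = 20%: 30 × 0.20 = 6 patients (20 points)
- With half detected in the test arm (s_T = 0.5): 0.75, 1.5 and 3 patients
- p_T = 0: no ascertainment effect at all

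**4. How often would the reference arm look worse with no true difference?** Assume p_R = p_T = p and s_R = 1. Recorded counts are then Binomial(30, p) in the reference arm and Binomial(30, p·s_T) in the test arm. With s_T = 0, the probability that the reference arm shows more is 1 − (1 − p)^30, for example 1 − 0.95^30 = 0.785. The other columns are exact sums over the two binomials.

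| True rate p, both arms | s_T = 0 | s_T = 0.5 | s_T = 1 |
| --- | --- | --- | --- |
| 5% | 0.785 | 0.555 | 0.377 |
| 10% | 0.958 | 0.688 | 0.413 |
| 20% | 0.999 | 0.821 | 0.436 |

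With equal detection the opposite ordering has the same probability (the remainder is ties). With unequal detection the balance shifts against the reference arm. This shows direction under an equal-rates assumption and is not an estimate for this trial.

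**5. Cardiovascular side.** If 10% of Cosopt-S patients developed a slow pulse or low pressure without symptoms (an assumption), 30 × 0.10 = 3 patients could go unseen under the present schedule.

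**The case against.** The strongest reply is that most of a potassium difference would be genuine. Section 1.1 attributes potassium depletion to oral acetazolamide and says tests and replacement are often needed. Section 4.1.2 reports that dorzolamide was not associated with acid-base disturbances in clinical studies. Monitoring also belongs to the reference regimen, so needing replacement is a legitimate burden to report against it. This stands, and it makes p_T, and with it the ascertainment term, possibly small.

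Two stronger readings should be resisted. A reader might infer that every replacement in the reference arm is an artefact of looking. Step 3 shows that this would need the same true rate on Cosopt-S, which the protocol does not suggest. A reader might also infer that no test-triggered AE can occur on Cosopt-S. That is wrong: the AE definition applies to both arms, AEs and health changes are asked about at Visits 2 to 6, and section 6.2.1.7 covers clinically significant laboratory values in any patient. Nor is it certain that every replacement would be recorded as an AE, since section 6.3.2 deals with it as a concomitant treatment.

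It can further be said that pulse and blood pressure are missing from both arms, so this is under-detection rather than unequal measurement; that symptomatic cardiovascular events remain reportable; that section 7.3.2 makes all secondary analyses exploratory; and that the MedDRA tables and the listing already let a reader pick out laboratory terms. All of this is correct and limits the weight of the point. It does not remove the pooling: the stated subcategories are intensity and relationship, not how the event was found. The visit schedule and the AE definition are protocol content, so they are not simply left to an analysis plan.

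**Conclusion.** The point holds in limited form. Potassium follow-up on treatment is specified for one arm only, its results can become AEs, and these are counted with symptom-based AEs towards a directional safety aim. Part of any between-arm difference can therefore be ascertainment. Its size cannot be computed from the protocol. It is bounded by the true rate of such events on Cosopt-S, and much of a potassium difference may be a real drug effect.

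Separately, the schedule does not match the cardiac exclusion and the named timolol effects, so silent effects of the test drug can be missed. Here too, unmeasured means unscheduled and not undetectable.

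No test or significance level is affected. This is a cheap improvement to a descriptive comparison. It rests on reading potassium replacement as an intervention under section 6.2.1.1, and on there being no routine laboratory follow-up in the test arm beyond what the protocol states.

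**What to change.** 1. In section 7.4, tabulate AEs triggered only by a test result separately from symptom-based AEs, by arm. State that the descriptive tolerability comparison rests on findings sought alike in both arms. Potassium findings and replacement remain reported, as a feature of the reference regimen. Cost: one extra table and a marker for how each AE was found. No new measurement is needed.

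2. Reconcile the schedule table and section 5 with the cardiac exclusion in section 3.6.2 and the timolol effects in sections 4.1.2 and 4.1.4. One way is to record pulse and blood pressure in both arms at the existing Visits 1 and 2, as a data item only and with no clinical rule attached, and to tabulate the change by arm. Cost: a few minutes at two visits and extra eCRF fields, with perhaps a few more asymptomatic findings. This does not address the potassium asymmetry, so it complements the first change and does not replace it.
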